## Abstract

**Background:**

Detection of circulating tumor DNA (ctDNA) is a promising method for postoperative surveillance of lung cancer. However, relatively low positive rate in early stage patients restricts its application. Aberrant methylation of ctDNA can be detected in blood samples, and may provide a more sensitive method. This study is designed to systematically evaluate and compare the detection of aberrant methylation and mutations in ctDNA among surgical non-small cell lung cancer (NSCLC) patients, aiming to investigate the feasibility of ctDNA detection as a means of lung cancer surveillance.

**Methods:**

This is a prospective observational study. Consecutive surgical NSCLC patients will be recruited. Blood samples will be collected both before and after surgery (during the follow-up period), while matching tumor tissues and tumor-adjacent normal tissues will be collected during surgery. Quantitative analysis of aberrant methylation and mutations of ctDNA will be conducted in combination with a three-year follow-up data.

**Discussion:**

This is the first registered prospective study designed to investigate the feasibility of ctDNA methylation detection as a means of postoperative lung cancer surveillance. We will systematically evaluate and compare the quantitative detection of ctDNA mutations and ctDNA methylation in surgical NSCLC patients, combining with the follow-up information. By integrating genetic and epigenetic information of ctDNA, more effective strategies for postoperative surveillance may be defined.

**Trial registration:**

This study (MEDAL, MEthylation based Dynamic Analysis for Lung cancer) was registered on ClinicalTrials.gov on 08/05/2018 (NCT03634826; Pre-results).

## Background

Lung cancer is the leading cause of cancer related death worldwide [1]. Although some early stage patients can get long-term disease free survival after curative surgery, there are still 20–40% stage I/II patients who suffer local recurrence or distant metastasis [2]. Patients with the same TNM stage may achieve greatly differential outcomes, indicating there are heterogeneities and traditional staging system might not be adequate. For postoperative patients, clinical visits and CT (Computed Tomography) are recommended as a principal means of tumor supervision [3]. However, although CT scans could detect disease progression earlier than X-ray for postoperative patients, overall survival of the two groups showed no statistical significance, indicating that traditional radiological methods may have already reached the limit and this probably due to the delay of early diagnosis and treatment. How to identify minimal residual disease (MRD) after curative surgery, as well as predict and detect recurrence without delay, still remains elusive.

Circulating tumor DNA (ctDNA) is a kind of tumor-specific DNA derived from tumor cells, which in principle contains the same genetic information of tumor tissue [4]. Detection of ctDNA with peripheral blood samples has been reported in different tumor types, especially in patients with advanced stage [5–7]. The eliminating rate of ctDNA is relatively high, making it an ideal biomarker to reflect tumor burden and providing a potential method for tumor management [4, 8–10]. In the field of non-small cell lung cancer (NSCLC), ctDNA has already shown its significance and gradually been recognized as a way to guide clinical practice [11–13]. However, previous researches focused mainly on patients of advanced stage (stage IIIB to IV). Studies of surgical patients (stage IA to III) were relatively rare, and data from early stage patients (stage IA to IIB) was especially scarce [14–16]. In addition, the amount of ctDNA is extremely low in early stage patients, increasing the difficulty of detection by sequencing, especially when there is a large amount of background cell free DNA (cfDNA) [4]. Although some institutions have explored the possibility of MRD detection after surgery, the sensitivity of ctDNA in early stage patients is not satisfying [17, 18]. In the recently published TRACERx study, the positive rate of ctDNA detected in stage I lung adenocarcinoma was only 19% [17]. To overcome these limitations, exploring multi-omics data may provide a promising strategy, such as integrating genetic and epigenetic information of ctDNA.

Methylation is one of the most common epigenetic alterations [19]. Methylation of CpG dinucleotide-rich clusters of gene promoter regions can cause gene silencing, which plays a significant role in the initiation and progression of malignant tumors.^6 19^ Previous studies indicated that aberrant methylation of DNA can be a promising biomarker. Brock et al. [20] illustrated a panel of 4 aberrant methylated genes, which were related to the recurrence of postoperative lung cancer patients. Recently, Akira et al. [21] demonstrated a different gene panel of methylation which could predict prognosis of NSCLC. In addition, aberrant methylation is often an early event in carcinogenesis and is detectable in blood samples [4]. With limited published researches, it seems that detection of methylated ctDNA can be a more sensitive method in early stage NSCLC patients [21]. However, most previous studies focused on the methylation of tumor tissues, while methylation of ctDNA in blood samples hasn’t been well illustrated [19, 20]. In the field of lung cancer, researchers explored different candidate genes or gene combinations, while an optimal panel of methylation still remains to be discovered [20, 21]. Besides, although ctDNA methylation has shown its potential of diagnosis and prognostic prediction value in several studies, some basic characteristics of ctDNA methylation still remains to be confirmed by prospective studies.

Conclusively, detection of ctDNA mutations as well as aberrant ctDNA methylation can be a promising way for the surveillance of NSCLC, and calls for further studies.

### Previous work

The detection of ctDNA in late stage lung cancer has been well illustrated by previous studies. To evaluate the feasibility of ctDNA detection in surgical NSCLC patients, we enrolled 76 NSCLC patients who underwent curative-intent lung resection and analyzed their blood samples as well as tumor tissues using a 50 cancer related mutation panel. The overall concordance rate between plasma samples and tissue samples was 68.4%, and would increase according to TNM stage (stage I, 57.9%; stage II, 66.7%; stage IIIA, 90%, *P* = .043). Additionally, ctDNA was more sensitive compared with traditional tumor markers, and has higher predictive value than classic prediction models.^11 12^

Furthermore, we explored the stability and dynamic changes of ctDNA in surgical lung cancer patients. Plasma samples were obtained before (1 to 3 days) and during surgery for 20 patients. All ctDNA samples obtained before and during surgery had consistent mutations, and the mutation frequency varied at a very low level, indicating that plasma ctDNA offers reliable and consistent information. As dynamic changes of ctDNA in lung cancer patients remained to be clarified, we explored its half-life period and confirmed a rapid clearance after surgery. Three days after surgery was considered as an optimal start time for recurrence monitoring, as ctDNA concentration would reduce to zero theoretically. Interestingly, during the follow-up of postoperative patients, we found that ctDNA detection was in conformity with patients’ outcome [11, 12, 22].

To sum up, we have completed a series of studies in the field of liquid biopsy, demonstrated the feasibility of ctDNA detection in surgical NSCLC patients, and shown its potential value for postoperative surveillance.

### Hypotheses

For stage IA to III surgical NSCLC patients, blood samples and tumor tissues have high concordance for both DNA mutation and aberrant DNA methylation.Detection of ctDNA methylation has comparable, if not greater, sensitivity than that of ctDNA mutation in early stage patients.Quantitative changes of ctDNA mutation and its aberrant methylation can be used to predict patients’ prognosis, and can reflect tumor progression earlier than radiological examinations.

### Primary aims

To investigate the relationship between surgical lung cancer patients’ prognosis and quantitative changes in ctDNA mutations and aberrant methylation.To investigate the variation of aberrant methylated ctDNA concentration before surgery, 3 days after surgery and 1 month after surgery.

### Secondary aims

To analyze the conformity of DNA mutation and aberrant DNA methylation between blood samples and tumor tissues of stage IA to III surgical patients.To illuminate the characteristics and relationship of tumor DNA methylation, ctDNA methylation, and tumor-adjacent normal tissues methylation.To classify stage IA to III surgical patients by genetic changes and signaling pathway changes, and to explore the relationship between molecular characteristics and postoperative DFS.For patients who receives adjuvant therapy, to investigate the consistency of postoperative DFS and the variation in abundance of ctDNA mutations or aberrant methylation.To evaluate whether detection of ctDNA methylation and mutations can predict tumor progression earlier than radiological examination in some patients, and illustrate its leading time.

### Methods/design

This protocol outlines a prospective observational study (MEDAL, MEthylation based Dynamic Analysis for Lung cancer) in which surgical NSCLC patients will be recruited. Blood samples will be taken before and after surgery, while tumor tissue samples and tumor-adjacent normal tissues will be collected during surgery. Patients recruited will be followed for at least three years after surgery (Fig. 1).

**Fig. 1 Fig1:**
[figure not shown]
Flow chart of patient recruitment, sample collection and follow-up

### Study population

The population will be recruited from Peking University People’s Hospital Thoracic Surgery Department. All of the patients will receive thoracic CT scans (with or without contrast), abdominal and adrenal gland ultrasonography or CT, brain MRI (Magnetic Resonance Imaging) or CT and radionuclide bone scan before surgery. Positron Emission Tomography (PET/CT) will not be mandatory. Traditional tumor markers will be examined, including carcinoembryonic antigen (CEA), carbohydrate antigen 125 (CA-125), carbohydrate antigen 199 (CA-199), cytokeratin 19 fragment (CYFRA21-1), neuron-specific enolase (NSE), and interleukin 6 (IL-6). Consecutive patients who are suspected stage IA- III NSCLC before surgery will be eligible and included in this study. Patients who will be enrolled in this study should meet the following conditions: (1) Radiology examinations suspects lung cancer, and patients who will be treated by curative surgery. (2) Suspected stage between IA to III. (3) Understand and agree with the informed consent. The exclusion criteria are as followed: (1) Patients with pure ground glass opacity (pGGO). (2) Have received chemotherapy, radiotherapy, targeted therapy, or immunotherapy before surgery. (3) Malignant tumor history within the past 5 years. (4) Multiple primary lung cancer and can’t be resected completely. (5) Pathology of frozen sections or paraffin sections proves the tumor is not NSCLC. (6) Pathological stage proves to be IIIB-N3 or IV. (7) Samples of blood or tissues are unqualified or cannot be obtained. (8) Refuse to sign the informed consent.

Follow-up information will be obtained 1 month after surgery and every 3–6 months thereafter by an experienced thoracic surgeon. The follow-up protocol consists of chest CT scan and abdominal ultrasound performed every 6 months for the first 2 years and yearly thereafter. Traditional tumor markers will be examined every 6 months. Brain MRI or CT and radionuclide bone scan will be performed when patients have symptoms.

Clinical and demographic data will be collected, including age, sex, smoking status, past medical history, family history of cancer, radiological reports, tumor markers, pathology reports and postoperative TNM-staging.

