### Sample collection

20 mL blood samples will be taken by intravenous puncture at different time points. Patients recruited to this study will have their blood samples taken for at least 3 times (Blood Sample A: Before surgery; Blood Sample B: Three days after surgery; Blood Sample C: One month after surgery). Patients whose blood samples are not gathered for any of these 3 time-points will be excluded for analysis. During the follow-up period, recruited patients’ blood samples will also be gathered when thoracic CT scans are performed.

Tumor samples (Sample T) will be collected during surgery after intraoperative frozen section proves to be malignant (NSCLC). To analyze the methylation characteristics of normal lung tissue of NSCLC patients, two samples of tumor-adjacent normal tissues will be collected separately. We will collect normal tissues which are 2 cm (Sample N2) and 5 cm (Sample N5) away from the edge of tumor. Sample N5 will not be mandatory, for some patients may have wedge resection and the surgical specimens are relatively small. All the tissue samples will be stored at − 80 °C until analysis.

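### The planned ctDNA lead over radiology mixes scheduled chest and abdominal imaging with symptom-triggered brain and bone imaging; for brain and bone relapses the lead is partly lead over symptoms

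*Protocol article*

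**What the plan says.** The third hypothesis (Hypotheses) is that quantitative ctDNA changes "can reflect tumor progression earlier than radiological examinations". The last secondary aim (Secondary aims) is to evaluate whether ctDNA "can predict tumor progression earlier than radiological examination in some patients, and illustrate its leading time". Neither statement separates relapse sites or ways of detecting relapse.

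The follow-up schedule (Study population) consists of "chest CT scan and abdominal ultrasound performed every 6 months for the first 2 years and yearly thereafter". For the remaining sites, "Brain MRI or CT and radionuclide bone scan will be performed when patients have symptoms". Every patient does have "brain MRI (Magnetic Resonance Imaging) or CT and radionuclide bone scan before surgery", so brain and bone are examined in everyone at baseline but not on a schedule afterwards.

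Blood follows the chest schedule (Sample collection): after "Blood Sample B: Three days after surgery; Blood Sample C: One month after surgery", "recruited patients’ blood samples will also be gathered when thoracic CT scans are performed". Under Methods/design, "Patients recruited will be followed for at least three years after surgery".

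**The concern.** A lead time is the gap between two detection dates, so it depends on how each date comes about. For a chest relapse, blood and CT are taken at the same visit, and the comparison is like for like. For a brain or bone relapse, blood is still drawn on schedule, but the imaging date waits for symptoms. Part of the gap then reflects the absence of a scan rather than the speed of the assay.

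The aim asks only whether ctDNA is earlier in some patients, which a handful of such relapses could satisfy. The Duration of study and Discussion sections plan to derive a surveillance strategy from the results. A reader would take a lead over radiology to mean that the assay outperforms a scan.

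**Working it through.** **The plan's own figure.** The lead-time aim has no stated size. The only design figure is power over 90% for DFS at alpha 0.05 (Sample size calculation). It reproduces with two-sided alpha, which is an assumption because the article does not state the side:

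- Two proportions, 50% vs 10%, 15:85 split: power 99.7% with 200 patients, 99.2% with 200 × 0.85 = 170.
- Schoenfeld, HR = ln 0.5 / ln 0.9 = 6.58: one-year events 30 × 0.5 + 170 × 0.1 = 32 give 96.7%; with 170 patients, 27.2 events give 93.9%.

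The present point does not rest on this figure.

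**Direction.** Compare two imaging rules for the same brain or bone site: symptoms only, and symptoms plus the scheduled visits. Adding scheduled visits can only bring the imaging date forward or leave it unchanged. Symptom-only imaging can therefore only lengthen the apparent lead or leave it unchanged. This follows from the schedule and needs no assumed rate.

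**Size per affected relapse.** Assumptions, none of them in the document:

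- The lesion becomes visible to imaging at a uniformly distributed time.
- Symptoms follow S months later.
- Tests are perfect.

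With 6-monthly visits, the wait U from visibility to the next visit is uniform on 0 to 6 months. If U < S, the visit comes before the symptoms and symptom-only imaging is S − U months later than scheduled imaging would have been. Otherwise the two dates coincide. The mean excess is

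E[max(S − U, 0)] = S²/(2 × 6) = S²/12 for S up to 6 months, and S − 3 beyond that.

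- S = 3: 9/12 = 0.75 months
- S = 6: 36/12 = 3 months
- S = 9: 9 − 3 = 6 months; S = 12: 12 − 3 = 9 months (wider range, for orientation)

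A simulation with blood at months 1, 6, 12, 18, 24 and 36, scheduled imaging at the same times except month 1, and visibility uniform over months 0 to 24 gave the same excesses. They were identical for a true ctDNA lead of 0, 3 or 6 months. With no true lead:

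| Symptom lag | Mean lead, scheduled + symptoms | Mean lead, symptoms only | Relapses with any lead |
|---|---|---|---|
| 3 months | 0.10 | 0.85 | 4% → 54% |
| 6 months | 0.21 | 3.21 | 4% → about 100% |

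The 4% arises because the month-1 blood sample has no scan beside it.

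Under the yearly schedule after year 2, the same formula gives S²/24: 0.375 months at S = 3 and 1.5 months at S = 6.

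**Size in a pooled mean.** Assume 20 to 40% of first relapses are in brain or bone:

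- low: 0.20 × 0.75 = 0.15 months
- high: 0.40 × 3 = 1.2 months

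**How many patients.** Only ctDNA-positive patients who relapse can show a lead. The Sample size calculation assumes 15% positive and 85% followed: 200 × 0.15 × 0.85 = 25.5. If half of these relapse (12.75), a 20 to 40% share is about 3 to 5 patients; if all relapse, about 5 to 10.

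**The case against.** The strongest reply is that the comparator is legitimate. The Background describes clinical visits and CT as recommended surveillance, and the Discussion aims to integrate liquid biopsy with current practice. Lead over imaging as actually delivered is a fair surveillance question. That stands, provided the figure is labelled so; it does not support a claim of lead over radiological examination in general.

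Second, no pooled mean or test is written down. The aim is descriptive, and a split by site could sit in a fuller document. This stands in part: pooling is implied by an undifferentiated comparator, not stated. But nothing shown corrects the asymmetry, and the Discussion concedes follow-up bias only in general terms.

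A reader might infer more than the documents support:

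- *That ctDNA always comes first in these relapses.* It does not. A lesion that becomes symptomatic between draws is imaged before the next sample. With no true lead and a 3-month lag, ctDNA is first in 54% of them in the simulation, and in about 3/12 = 25% once visits are yearly.
- *That the whole symptom lag becomes lead.* That would give 0.20 × 3 = 0.6 to 0.40 × 6 = 2.4 months pooled, but it treats blood as drawn continuously. The size depends on the sampling interval; only the direction does not.
- *That silent lesions would be scored as ctDNA false positives.* The article states no such rule. It compares specificity using the 3-year follow-up, by which time a patient who has relapsed counts as a relapse. Exempting positive samples because of a later relapse would itself be an outcome-dependent rule favouring the assay.

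**Conclusion.** The point holds in a limited form. For first relapses in brain or bone, the apparent ctDNA lead over radiology is partly lead over symptomatic diagnosis. The direction follows from the document's own schedules. The size does not, because neither the share of such relapses nor the delay to symptoms is given. Under the assumptions in the working, the excess is about 0.75 to 3 months per affected relapse and 0.15 to 1.2 months in a pooled mean. An imperfect assay would make it smaller. A relapse that is also visible on the scheduled chest CT or abdominal ultrasound is not affected. The point touches one secondary aim and part of the third hypothesis, and leaves the DFS comparison that sized the study alone.

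**What to change.** - Base the claim of lead over imaging on first relapses at sites imaged on schedule, that is, chest and abdomen.
- Report first relapses found by symptom-triggered brain or bone imaging separately, labelled *lead over symptomatic diagnosis*.
- Record for each relapse the site and the mode of detection (scheduled or symptom-triggered).

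The cost is analysis wording and two data fields, obtainable from the radiology reports that the study already collects. The imaging and blood schedules stay as they are. The downside is fewer relapses behind the headline lead-time figure, in a set that is already small.

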### Sample collection

20 mL blood samples will be taken by intravenous puncture at different time points. Patients recruited to this study will have their blood samples taken for at least 3 times (Blood Sample A: Before surgery; Blood Sample B: Three days after surgery; Blood Sample C: One month after surgery). Patients whose blood samples are not gathered for any of these 3 time-points will be excluded for analysis. During the follow-up period, recruited patients’ blood samples will also be gathered when thoracic CT scans are performed.

Tumor samples (Sample T) will be collected during surgery after intraoperative frozen section proves to be malignant (NSCLC). To analyze the methylation characteristics of normal lung tissue of NSCLC patients, two samples of tumor-adjacent normal tissues will be collected separately. We will collect normal tissues which are 2 cm (Sample N2) and 5 cm (Sample N5) away from the edge of tumor. Sample N5 will not be mandatory, for some patients may have wedge resection and the surgical specimens are relatively small. All the tissue samples will be stored at − 80 °C until analysis.

### Plasma collection and cfDNA isolation

Whole blood samples (20 ml) from NSCLC patients will be collected in Cell-Free DNA BCT tubes (21,892, Streck) and processed within 24 h. The temperature for transportation will be maintained at 15–35 °C according to the manufacturer’s protocol. Plasma will be extracted by centrifugation for 10 min at 2200 x g followed by 15 min at 16,000 x g using a refrigerated centrifuge. Following centrifugation, the supernatant will be transferred into a clean polypropylene tube immediately and stored at − 80 °C for future analysis. Cell-free DNA will be extracted using the QIAamp Circulating Nucleic Acid kit (55,114, Qiagen). The concentration and size profiles of isolated DNA will be examined by Qubit 3.0 dsDNA HS assay (Thermo Scientific) and HT DNA high sensitivity Labchip (Perkin Elmer). All procedures will be performed according to manufacturer’s protocols.

### DNA library preparation and sequencing

The brELSATM library prep method will be used to create bisulfite sequencing library illustrated in Fig. 2. Briefly, extracted cfDNA will be treated with sodium bisulfite (D5046, EZ-96 DNA Methylation-Lightning™ MagPrep, Zymo Research), turning all cytosine to uracil while leaving 5-methylcytosine unchanged. Subsequently the converted single-strand DNA molecules will be ligated to a splinted adapter, and copies of the template strands will be generated in the presence of extension primers and a uracil-tolerating DNA polymerase. After a second round of adaptor-ligation to the copy strands, 10–14 cycles of PCR reactions will be applied to obtain whole-genome BS-seq libraries. Custom-designed lung-cancer methylation profiling RNA baits will be used for target enrichment. Following a 12–16 h hybridization step, biotinylated RNA probe-bound library fragments will be selectively enriched and amplified with 14 PCR cycles. The target libraries will then be quantified by real-time PCR (Kapa Biosciences) and sequenced on NovaSeq 6000 (Illumina) using 2 × 150 bp cycles.

